### Interventions

Participants allocated to the intervention conditions (i.e., self-directed use of ClearlyMe® and guided use of ClearlyMe®) will be instructed to complete the ClearlyMe® app content by undertaking at least one collection per week (approximately 20 minutes in duration) for 6 weeks; however, participants can complete the app content in any order and according to their preferences. Participants will also be instructed to use the ‘Get Help’ section of the ClearlyMe® app if they feel they require extra mental health support during the intervention period, although this is not monitored by the research team. To promote compliance, participants allocated to this condition will be sent weekly SMS reminders (total of 6) to use the app. The ClearlyMe® app also includes an in-built ‘revisit the app’ reminder, which notifies participants to use the app after 7 days of inactivity. Participants who allow notifications during the app’s onboarding will receive these reminders but can deactivate it at any time via their mobile phone settings. Participants who fail to download the ClearlyMe® app within 7 days of randomisation will be sent one email and one SMS reminder to download the app. Participants who do not download the app will remain in the trial and be included in the intention to treat analyses.

Participants in the Guided use of ClearlyMe® condition will also receive a weekly guided support session delivered outside of school hours via Short Message Service (SMS) by a member of the research team using a standard script and decision flow chart (see Additional File 1). Research Assistants (RAs) will be trained to conduct these sessions and will be supervised by an experienced clinical psychologist. These sessions will consist primarily of technical support with some low intensity motivational coaching to encourage app use. The chat sessions are designed to take place in one sitting (i.e., approximately 20 minutes) but given the nature of SMS communication, will occur until the script is completed. Duration and script compliance will be recorded. Chat sessions will be prescheduled to take place between 3:30 pm and 6 pm on Mondays to Fridays. For non-responsive participants, the research team will instigate one additional contact attempt, made within 2 days of the initial attempt, however, the weekly chat schedule will remain unchanged, regardless of when a participant responds. Participants in this condition will be provided an additional $25 reimbursement for phone credit upon allocation to the guided support condition.

### Control condition

This study will utilise an active attention-matched control condition consisting of digital psychoeducation flyers. Attention-matched control conditions account for nonspecific intervention effects and are frequently used in other studies within the digital health field [39]. Psychoeducation is a known and acceptable intervention for young people that has demonstrated small positive effects on mental health without containing active CBT elements [40–42]. It is also information frequently consumed by young people during autonomous digital help seeking [36]. Digital psychoeducation in the current study has been designed to be comparable to the intervention conditions in terms of weekly dosage of content, activities, visual appeal, and duration to complete. These factors ensure digital psychoeducation satisfies both ethical and methodological requirements and has the potential to reduce control condition dropout [43]. Participants allocated to this condition will receive six weekly psychoeducation flyers, delivered via SMS that contains a URL to a static Portable Document Format (PDF). Participants are required to click the URL to access the flyer directly on their mobile device. The psychoeducation consists of six topics (taking approximately 20 minutes to read) containing information on mental health problems, links to credible Australian mental health organisations, and suggested activities for self-care. The content was created by the Black Dog Institute and used in other mental health studies among adolescents [41, 42]. Participants in this condition will not receive any additional contact from the research team, unless technical support (requested via email) is required. Engagement with the psychoeducation flyers will be determined by recording the number of times an individual participant clicks the flyer link, including time and date of access. Post-trial, participants in this condition will receive one email that includes a collated PDF containing all the psycho-education material in one file for future use. Participants will be instructed to use the ‘Get Help’ section of the study site if they feel they require extra mental health support during the study period, although this will not be monitored by the research team. All participants in the control condition will be provided with 6-weeks access to ClearlyMe® once their participation in the trial has concluded.

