## Abstract

**Background:**

Depression is a leading cause of disability in adolescents, however few receive evidence-based treatment. Despite having the potential to overcome barriers to treatment uptake and adherence, there are very few CBT-based smartphone apps for adolescents. To address this gap, we developed ClearlyMe®, a self-guided CBT smartphone app for adolescent depression and anxiety. ClearlyMe® consists of 37 brief lessons containing core CBT elements, accessed either individually or as part of a ‘collection’. Here, we describe the protocol for a randomised controlled trial aiming to evaluate the effect of ClearlyMe® on depressive symptoms and secondary outcomes, including engagement, anxiety and wellbeing, when delivered with and without guided support compared to an attention matched control.

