### Hypotheses

The primary hypothesis is that relative to the attention control condition, participants who receive the ClearlyMe® app (self-directed or guided) will have greater reductions in self-reported depressive symptoms between baseline and 6-weeks post-baseline (primary endpoint), as well as baseline and 4-month follow-up (secondary endpoint). A secondary hypothesis is that relative to the control condition, participants who receive the ClearlyMe® app (self-directed or guided) will report greater improvements in anxiety symptoms, psychological distress, emotional wellbeing, quality of life, rumination, emotion regulation and CBT skill acquisition between baseline and 6-weeks post-baseline, as well as baseline and 4-month follow-up. It is hypothesised that participants who receive guided support to use ClearlyMe® will report significantly higher levels of engagement than those who do not, however, no hypotheses have been made regarding the effect of guided support on outcomes given mixed findings in the literature e.g. [19, 21, 30, 35]. Exploratory analyses will examine whether the intervention was more effective for certain subgroups of the sample (e.g., based on age, symptom severity at baseline, greater perceived need for care, and higher openness to digital mental health) and whether the effects of the intervention were driven by other variables, such as rumination, emotion regulation, CBT skill acquisition, digital therapeutic alliance, and measures of app engagement.

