### Strengths

The design of the MobiliseMe trial is robust. First, the inclusion of an active-attention matched control condition will allow an evaluation of the impact of ClearlyMe® over and above the support young people commonly receive when help-seeking independently, that is, information about mental symptoms and treatment options [93]. Second, a comparison condition that involves using ClearlyMe® with SMS guidance is well-matched to the needs of young people [31, 32] and will provide much needed knowledge on the influence of guidance on engagement and effectiveness. Third, the sample size (*N* = 489) of the trial will ensure adequate power to detect intervention effects. Finally, a thorough consideration of ‘engagement’ and transparent reporting of how constructs such as uptake, adherence and completion have been operationalised, measured and analysed addresses a well-documented limitation in the field [22, 67, 88, 94].

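### The control is presented as attention-matched to both app arms, but on scheduled time and human contact it matches only the self-directed arm

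*Protocol article*

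**What the plan says.** The Control condition section calls the flyers an active attention-matched comparator and gives the reason: "Attention-matched control conditions account for nonspecific intervention effects". It states the scope of the match in the plural; the flyers were "designed to be comparable to the intervention conditions in terms of weekly dosage of content, activities, visual appeal, and duration to complete". The Interventions section uses that plural for self-directed and guided use together. The abstract (Background) says the app will be evaluated "when delivered with and without guided support compared to an attention matched control". The primary hypothesis follows the same pattern: "relative to the attention control condition, participants who receive the ClearlyMe® app (self-directed or guided) will have greater reductions".

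The arms are described as follows.

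- **Both app arms (Interventions):** at least one collection a week, about 20 minutes, for six weeks.
- **Guided arm only (Interventions):** in addition, a weekly SMS session with a trained research assistant working from a script. On length: "The chat sessions are designed to take place in one sitting (i.e., approximately 20 minutes". The content is mainly technical help with some coaching to motivate app use. A participant who does not reply gets one further contact attempt.
- **Control arm (Control condition):** one flyer a week by SMS link, with a reading time of about 20 minutes. "Participants in this condition will not receive any additional contact from the research team", apart from technical help requested by email.

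Under Strengths the article says that "the inclusion of an active-attention matched control condition will allow an evaluation of the impact of ClearlyMe® over and above the support". The sentence goes on to define that support as information young people find for themselves. The Limitations section does not mention the extra contact in the guided arm.

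**The concern.** An attention control is there to hold constant the time and contact that come with an intervention, so that a remaining difference can be credited to the active content. If one of the two app arms has more of both, the label does not license that conclusion for that arm.

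This matters because the primary hypothesis names either app arm against the same attention control. If guided use beat control and self-directed use did not, the present wording would allow the result to be reported as the app outperforming an attention-matched comparator, although the added contact would remain an open explanation. The article itself treats support as able to change outcomes. Its Background cites evidence, with contrary findings noted, that human support goes with better outcomes, and its Sample size section plans a larger effect for guided than for self-directed CBT.

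**Working it through.** The plan gives no total for contact time, so there is no figure of its own to reproduce. The check adds up the scheduled minutes stated for each arm.

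**Formula:** scheduled total = (content minutes per week + session minutes per week) × 6 weeks.

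| Arm | Content/week | Live session/week | Six-week total | Ratio to control |
|---|---|---|---|---|
| Control | 20 | 0 | 20 × 6 = 120 | 1.0 |
| Self-directed | 20 | 0 | 20 × 6 = 120 | 120/120 = 1.0 |
| Guided | 20 | 20 | (20 + 20) × 6 = 240 | 240/120 = 2.0 |

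**One reading to settle.** The 20 minutes for the flyers is taken as the time per weekly flyer, which fits the article's statement that weekly dosage and duration were made comparable. If it meant all six topics together, control would total 20 minutes and the ratios would be 120/20 = 6 and 240/20 = 12. The mismatch for the guided arm would then be larger, and the self-directed match would fail as well.

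**Human contact.** Control: none scheduled. Self-directed: none scheduled. Guided: six sessions with a research assistant.

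**What each contrast isolates.**

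- Self-directed versus control: app against flyers, with scheduled time equal and no live sessions on either side.
- Guided versus self-directed: the effect of adding support to the app.
- Guided versus control: app plus support against flyers. Time and contact differ along with the content.

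**Planned differences.** From the within-group effects in the Sample size section (0.10, 0.35, 0.65):

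- self-directed minus control: 0.35 − 0.10 = 0.25
- guided minus control: 0.65 − 0.10 = 0.55
- guided minus self-directed: 0.65 − 0.35 = 0.30

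These show only that the time-matched contrast is the one with the smaller planned difference.

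**The case against.** The best defence is that the matching claim is about materials. The properties listed are content dosage, activities, visual appeal and duration, and a 20-minute flyer does correspond to a 20-minute collection in either app arm. Human contact is not listed as matched, and the article openly describes the weekly chats and the absence of contact in the control arm. This explains how the wording arose. It does not rescue the general label, or the statement about nonspecific effects, both of which are applied without excepting the guided arm.

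The second defence is that three arms already separate app from support. This stands. Self-directed versus control remains time-matched, guided versus self-directed estimates the added support, and the article makes no hypothesis about the effect of guidance on outcomes. The design is sound; the fault lies in how one contrast is labelled.

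Third, the Strengths sentence read to its end claims a comparison with self-sought information, which flyers represent fairly for both app arms. This also stands.

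Fourth, the sessions are scripted SMS exchanges, mainly technical, and their actual length is recorded and may differ from 20 minutes. This is a fair caution about size, but they are still individual human contact that the control arm lacks.

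**Conclusion.** The article states a design property that one of its two app-versus-control contrasts lacks. On scheduled time the guided arm has about twice the control dose (240 against 120 minutes), plus six live sessions against none. This assumes that the 20 minutes applies to each flyer and that sessions run to their planned length. No estimate, error rate or sample size changes; what changes is the conclusion that guided versus control can support.

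A reader might infer several stronger things that the document does not support.

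- **That 55% of the planned guided effect (0.30/0.55) is due to guidance and not the app.** The planning effects come from different cited sources and are not offered as additive parts. The coaching is meant to increase app use, so some of the 0.30 could act through the app.
- **That guided versus control is the only well-powered contrast, or that a guided-only result is the likeliest.** With 489/3 × 0.8 ≈ 130 per arm, an unadjusted two-sample comparison has about 99% power at 0.55 and 52% at 0.25. The planned model uses repeated measures. If the effects are on the raw-score scale and baseline is adjusted for, power at 0.25 is about 64% at an assumed correlation of 0.5 and about 80% at 0.7. The article gives no correlation.
- **That attention would explain a guided effect equally well.** The documents show only that the two cannot be separated in that contrast.
- **That the $25 is an unmatched incentive.** The article says that it covers the cost of the text messages.

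**What to change.** - In the abstract, Hypotheses and Control condition sections, limit the attention-matched description to the self-directed arm.
- Rest any claim of an app effect beyond nonspecific attention on self-directed versus control.
- Describe guided versus control as the effect of the app plus human support, and guided versus self-directed as the effect of adding support.
- Add to Limitations that guided versus control differs in scheduled time and human contact as well as content.
- Leave the Strengths sentence as a comparison with self-sought information, provided that it does not imply attention matching for the guided arm.

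This is a change of wording, with no effect on arms, assessments, sample size or models. The cost is that the app-only claim rests on the contrast with the smaller planned difference, 0.25 against 0.55.

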### Procedure and participant timeline

Table 1 outlines the schedule of enrolment, interventions and assessments and Fig. 1 the study flow. Interested adolescents will be directed to the study webpage and asked to undergo a short online screener to determine their eligibility. Participants who do not pass screening will be provided with mental health service information. Only eligible participants will be invited to review the online Participant Information and Consent Form (PICF; see here) and proceed to the baseline assessment. Once completed, participants will be asked to register to the study by creating an account on the Black Dog Institute Research Engine. Participants are required to provide their full name, email, mobile phone number, date of birth, and to create a password. Registered participants will then be invited to view the online Parent Participant Information and Consent Form (P-PICF), to be completed by their parent or guardian within 1 week. Participants will receive three reminders to submit the P-PICF. Upon completion of the parental consent form, parents will be automatically emailed a copy of the P-PICF. If an invalid parent email address is entered, the research team will be notified via the study inbox and will contact the participant via email to confirm their parent’s details. Once the P-PICF has been submitted, participants will be instructed to complete the baseline assessment within 7 days. Participants who do not provide full consent or complete their baseline assessment within the allocated time will be automatically withdrawn from the study.

**Table 1 Tab1:**
[figure not shown]
Schedule of enrolment, interventions, and assessments

^*^Assessed in intervention groups’ 1 and 2 only

^^^Assessed in intervention group 2 only

**Fig. 1 Fig1:**
[figure not shown]
Study flow

Upon completion of the baseline assessment, participants will be randomised to one of the three study conditions and receive the relevant intervention instructions via email and SMS. At 6-weeks post-baseline and at 4-months follow-up, all randomised participants will be invited via email and SMS to complete the study assessments. Participants will have 7 days to complete each assessment and will receive two reminders to do so. All study assessments will take approximately 20 minutes to complete and can be undertaken on any Internet-enabled device. Participants will be reimbursed 10AUD (electronic gift voucher) for each study assessment completed (30AUD total). In addition, participants receiving guided use of ClearlyMe® will receive 25AUD upon group allocation to cover the cost of sending and receiving SMSs. Discontinuation of the allocated intervention will occur if the participant withdraws from the trial or in the event that they are no longer able to engage in the intervention due to changed circumstances.

### Outcomes

#### Depressive symptoms

The primary outcome of this study is self-reported depressive symptoms as measured by the Patient Health Questionnaire-9 Adolescent version (PHQ-A) [44]. This 9-item self-report measure assesses the severity and frequency of depressive symptoms in the previous 14 days, with items rated on a 4-point Likert scale ranging from not at all (0) to nearly every day (3). Items are summed to produce a total score (range: 0 to 27) with higher scores indicating more severe depressive symptoms. Total scores will be used as the outcome measure, and can be classified into the following symptom severity categories: nil to minimal (0-4), mild (5-9), moderate (10-14), moderately severe (15-19), and severe (20-27). The PHQ-A is an adapted version of the validated PHQ-9 questionnaire [44, 45], has good psychometric properties for assessing depressive symptomology in adolescent populations [46–49] and has been endorsed for research and clinical evaluation with adolescents [44, 50, 51].

#### Generalized anxiety symptoms

This will be measured by the Generalized Anxiety Disorder-7 scale (GAD-7) [52]. This 7-item self-report measure assesses the severity and frequency of anxiety symptoms in the previous 14 days, with items rated on a 4-point Likert scale ranging from not at all (0) to nearly every day (3). Items are summed to produce a total score (range: 0 to 21) with higher scores indicating more severe anxiety symptoms. Total scores will be used as the outcome measure, and can be classified into the following symptom severity categories: nil to minimal (0-4), mild (5-9), moderate (10-14), moderately severe (15-19), and severe (20-27). The GAD-7 has good psychometric properties for assessing anxiety symptoms in adolescent populations [53, 54].

#### Psychological distress

This will be measured by the Distress Questionnaire-5 (DQ-5) [55]. This 5-item self-report measure assesses the frequency of psychological distress in the previous 30 days, with items are rated on a 5-point Likert scale, ranging from never (1) to always (5). Items are summed to produce a total score (range: 5 to 25) with higher scores indicating more severe psychological distress. The scale has established psychometric properties [55, 56] and has been used in adolescent populations [41, 57–60].

#### Emotional well-being

This will be measured by the Short Warwick-Edinburgh Mental Wellbeing Scale (SWEMWBS) [61, 62]. This 7-item self-report measures assesses individuals’ wellbeing in the previous 2 weeks, with items rated on a 5-point Likert scale, ranging from none of the time (1) to all of the time (5). Items are summed to produce a total score (range: 7 to 35) with higher scores indicating greater well-being. It has adequate psychometric properties to measure emotional wellbeing [63] in adolescent populations [64–66].

#### Quality of life

This will be measured by the Child Health Utility 9D (CHU-9D) [67]. This 9-item self-report measure assesses adolescents’ health related quality of life in nine domains of functioning including: worry, sadness, pain, tiredness, annoyance, schoolwork/homework, sleep, daily routine and ability to join activities. Each domain is rated on a 5-point scale, with each level representing increasing levels of severity within each domain e.g., I don’t feel worried today (1) to I feel very worried today (5). Items are summed to produce a total score (range: 9 to 45). The scale has good psychometric properties among adolescents [68–70] and can estimate quality adjusted life years for use in future cost-effectiveness evaluations of ClearlyMe® [71].

#### Rumination

This will be measured by the Ruminative Responses Scale – short version (RRS) [72]. This 10-item self-report measure assesses individuals’ tendency to engage in rumination. Individuals are asked to rate each item in response to the prefacing statement “what you generally do, not what you think you should do when feel down, sad or depressed”. The scale is composed of two subscales; reflection and brooding, with 5-items relating to each factor. Each item is rated on a 4-point scale ranging from almost never (1) to almost always (4). Items are summed to produce a total score (range: 10 to 40). Higher scores reflect higher levels of ruminative responses. The measure has good psychometric properties in adolescent populations [73–75].

